### Temperature control

From our previous study
[49], we estimated that 32% of bedsharing babies and 3.5% of cot sleeping babies had a core-peripheral temperature difference of <1°C after they had been asleep for 3.5 hours, suggesting thermal stress from a warm environment. About 40 babies per group are needed detect a difference of this magnitude with 90% power using the 5% level of significance. Ideally, babies should be neither too hot nor too cold; 75% of the cot-sleeping babies were in the ideal comfort zone, where the peripheral temperature is between -1°C and -3°C of the core temperature. Two groups of 98 babies have the potential to detect a difference of 20% with 80% power using the 5% level of significance.

### Breastfeeding

Currently, 45% of Māori babies are still breastfeeding at 3 months. In order to show a 20% increase in breastfeeding at 3 months (to 65%), 106 babies would be needed in each group to have 80% power using the 5% level of significance.

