**Methods/Design:**

This two arm randomised controlled trial is being conducted with 200 mother-baby dyads recruited from Māori communities in areas of high deprivation in the Hawkes Bay, New Zealand. They are randomised to *wahakura* or bassinet use and investigation includes questionnaires at baseline (pregnancy), when baby is 1, 3, and 6 months, and an overnight video sleep study at 1 month with monitoring of baby temperature and oxygen saturation, and measurement of baby urinary cotinine and maternal salivary oxytocin. Outcome measures are amount of time head covered, amount of time in thermal comfort zone, number of hypoxic events, amount of time in the assigned sleep device, amount of time breastfeeding, number of parental (non-feed related) touching infant events, amount of time in the prone sleep position, the number of behavioural arousals and the amount of time infant is awake overnight. Survey data will compare breastfeeding patterns at 1, 3, and 6 months as well as data on maternal mind-mindedness, maternal wellbeing, attachment to baby, and maternal sleep patterns.

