### Outcome measures

Primary outcome measures for the infant will be derived from the overnight sleep study (amount of time head covered, amount of time in thermal comfort zone, number of hypoxic events and amount of time in the sleep device) and from surveys (full or exclusive breastfeeding at 3 and 6 months). Secondary outcomes identified from the sleep study include number of infant head covering events, number of parental (non-feed related) touching infant events, amount of time in the prone sleep position, the number of behavioural arousals, and the amount of time infant is awake overnight.

Psychosocial factors will also be measured. Using questionnaires, maternal environmental chaos will be measured at baseline. Social support, and social and economic stress will be measured at baseline and 3 months. Maternal depression and change in depression (from baseline) will be measured at 3 months and 6 months. Parenting factors, including beliefs about infant care, attachment, and parenting adaptation will be measured at baseline and 3 months using both the questionnaires and maternal salivary oxytocin levels at baseline, 1 month and 3 months. Maternal mind-mindedness will be measured at baseline, 3 and 6 months, using the questionnaires, and an audio recording of the mother talking about her baby (see Table 
1).

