### Drop-out rate

After discussion with the midwifery group within which we will work, we estimate dropout of 5% at 1 month, 20% at 3 months, and 25% at 6 months. Our power studies are mainly dependent on the 1 month measures, so we will increase our required numbers by 5%.

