### Total numbers required

Overall, we believe that we should aim to recruit enough babies so that we have complete data at 1 month, of 100 babies per group – i.e. enrol 105 babies per group.

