#### Breastfeeding

Breastfeeding is a primary outcome for this study and information will be gathered from the questionnaires and the overnight sleep study. Participants will be asked at the baseline survey about their knowledge of breastfeeding and their intention to breastfeed. At 1, 3 and 6 months, participants will be asked questions about breastfeeding from which it will be possible to describe the frequency of breasfeeding, full, exclusive or partial breastfeeding, when breastfeeding ceased, and/or when solids or other milk were introduced. They will also be asked about their mothers’ and their partners’ support for, and attitudes toward, breastfeeding. The duration and timing of the breastfeeding episodes will be identified from the sleep study, as well as head covering events during breastfeeding.

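### Enrolling 105 per group leaves about 84 with 3-month breastfeeding data, not the 106 the protocol says 80% power needs, and the shortfall is not disclosed

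*Protocol article*

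**What the plan says.** The Outcome measures section lists "full or exclusive breastfeeding at 3 and 6 months" among the primary outcomes, and the Breastfeeding section under Measures repeats that "Breastfeeding is a primary outcome for this study". The Sample size section treats the breastfeeding proportion as the third major outcome.

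The Breastfeeding paragraph of the sample-size material takes 45% at 3 months as the current rate and 65% as the target, and concludes that "106 babies would be needed in each group to have 80% power using the 5% level of significance".

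On losses, the Drop-out rate section says "we estimate dropout of 5% at 1 month, 20% at 3 months, and 25% at 6 months". The next sentence gives the allowance made: "Our power studies are mainly dependent on the 1 month measures, so we will increase our required numbers by 5" per cent. Total numbers required then aims for 100 babies per group with complete data at 1 month, "i.e. enrol 105 babies per group". The abstract gives a different total: "This two arm randomised controlled trial is being conducted with 200 mother-baby dyads".

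**The concern.** The breastfeeding calculation refers to babies whose status is known at 3 months. The enrolment target of 105 per group is one below the 106 required even before anyone is lost, and the only allowance for loss is the 1-month figure. The 3-month figure, four times as large, stands in the preceding sentence and is not used.

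The protocol's third hypothesis expects significantly increased breastfeeding with the *wahakura*. If the trial finds no significant difference, a reader who goes to the sample-size section will see 106 per group and 80% power as the basis for this outcome. Nothing there says that the planned enrolment delivers less, or how much less.

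**Working it through.** **Inputs, all from the protocol article.** Rates 45% and 65%, 80% power and 5% significance (Sample size, Breastfeeding); loss of 20% at 3 months (Drop-out rate); 105 enrolled per group (Total numbers required); chi-squared comparison (Data analysis). Assumed: a two-sided test, equal groups, and the same 20% loss in each.

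**1. Reproduce the stated 106.** With p1 = 0.45, p2 = 0.65, mean 0.55, difference d = 0.20:

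- n = [1.960 × √(2 × 0.55 × 0.45) + 0.842 × √(0.45 × 0.55 + 0.65 × 0.35)]² / 0.20²
- n = [1.960 × 0.7036 + 0.842 × 0.6892]² / 0.04 = 95.9, so 96 per group without continuity correction.
- With the correction, n′ = (n/4) × [1 + √(1 + 4/(n × d))]² = 105.7, so **106 per group**.

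The stated figure is therefore right for a two-sided, continuity-corrected comparison. The same corrected formula gives 98 for 75% versus 55%, which matches the Temperature control paragraph, so the corrected method appears to be the one the authors used.

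**2. Babies expected at 3 months.** 105 × (1 − 0.20) = **84 per group**.

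**3. Power at 84 per group for 45% versus 65%.**

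- Standard error under no difference: √(2 × 0.55 × 0.45 / 84) = 0.0768. Under the alternative: √((0.2475 + 0.2275) / 84) = 0.0752.
- Uncorrected: Φ[(0.20 − 1.960 × 0.0768) / 0.0752] = Φ(0.659) = **74.5%**.
- Corrected, with the difference reduced by 1/84: Φ(0.501) = **69.2%**.
- Exact enumeration of the two binomials gives 75.3% and 70.1%.

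**4. Difference detectable with 80% power at 84 per group**, from 45%: 21.3 points uncorrected, 22.5 points corrected.

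**5. Sensitivity to the abstract's total.** If 200 are enrolled, 100 × 0.80 = 80 per group remain, and power is 72.4% uncorrected or 66.7% corrected.

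**6. Scale of the gap.** Having 106 per group at 3 months after 20% loss would need 106 / 0.80 = 132.5, so 133 enrolled per group.

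| Per group | Power, uncorrected | Power, corrected |
|---|---|---|
| 106 (stated need) | 83.8% | 80.1% |
| 105 (no loss) | 83.5% | 79.7% |
| 84 (105 less 20%) | 74.5% | 69.2% |
| 80 (100 less 20%) | 72.4% | 66.7% |

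**The case against.** The strongest reply is that the protocol makes no false claim. The breastfeeding sentence is conditional: it says what would be needed, not what the trial will have. The authors then say openly that they size mainly on the 1-month measures, and 100 babies with complete 1-month data covers the 88 and 98 per group stated for head covering and thermal comfort. A careful reader can find the 106, the 20% and the 105 close together. All of this stands, so a reader who inferred that the protocol asserts 80% power for breastfeeding at 105 enrolled would go too far. What remains is that the reduced power for a declared primary outcome is neither stated nor quantified.

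The shortfall is also moderate. Data analysis names a chi-squared test without mentioning a continuity correction. Uncorrected, 96 per group would suffice and power at 84 is about 75%, so 69% is the less favourable end. Even that more favourable method falls short of 80%. The discrete time model planned for breastfeeding might use 1-month information from dyads lost later, but the gain cannot be worked out from the document, and the 106 belongs to a two-proportion comparison. The modified intention-to-treat set keeps anyone with one follow-up visit, which does not supply a missing 3-month outcome.

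Two further inferences are tempting and not supported. One is that breastfeeding is the only primary outcome on which benefit is hoped for. Time in the sleep device is also primary, and the second hypothesis predicts less same-surface bedsharing with the *wahakura*. The other is that 6-month breastfeeding ought to become secondary. That would change a declared primary outcome in a trial already under way, and correcting a power statement does not require it.

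**Conclusion.** The point holds as an undisclosed shortfall. The 106 is correct in itself, but by the protocol's own loss estimate the enrolment target yields about 84 babies per group at 3 months. Power for 45% versus 65% is about 69% on the method that reproduces 106 and about 75% without continuity correction; 80% power is available only for about 21 to 22.5 points rather than 20.

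This assumes a two-sided 5% test, equal allocation, 20% loss in each group, and no recovery of missing 3-month outcomes by modelling. The conclusion that power is below 80% does not depend on which formula is chosen.

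The difference between 200 and 210 dyads is a minor inconsistency. The 200 may mean 2 × 100 babies with complete 1-month data, but the abstract describes them as recruited.

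**What to change.** Keep enrolment unchanged and add to the Sample size text, after the breastfeeding calculation or under Total numbers required, a statement such as:

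> With 105 enrolled per group and 20% loss, about 84 per group are expected to have breastfeeding data at 3 months. This gives about 69% power (continuity-corrected) to 75% power (uncorrected) for 45% versus 65%, or 80% power for a difference of about 21 to 22.5 percentage points.

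In Drop-out rate, keep the sentence on 1-month measures, which is true and explains the 5%, and qualify it: the inflation covers the sleep-study outcomes and not breastfeeding at 3 months.

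Use one enrolment total in the abstract and the sample-size section, or say that 200 is the number expected with complete 1-month data and 210 the number to enrol.

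The cost is wording only. No participants are added and no outcome changes status; the power shown for breastfeeding becomes less favourable.

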### Drop-out rate

After discussion with the midwifery group within which we will work, we estimate dropout of 5% at 1 month, 20% at 3 months, and 25% at 6 months. Our power studies are mainly dependent on the 1 month measures, so we will increase our required numbers by 5%.

### Total numbers required

Overall, we believe that we should aim to recruit enough babies so that we have complete data at 1 month, of 100 babies per group – i.e. enrol 105 babies per group.

### Data collection and transfer

A unique feature of this study is that it assesses a Māori-derived intervention and that recruitment and data collection will occur in an area of New Zealand with a high Māori population, with high levels of deprivation, and by researchers who are Māori with connections to the local community.

Data files of 20 Gbytes/study will be transfered from the study area to the University of Otago using the New Zealand eScience infrastructure (NeSI) high speed KAREN network. The Autonomy TeleForm system (Autonomy Inc, San Francisco, CA94105, USA) will be used to create machine-readable survey forms. Completed surveys will be scanned and sent electronically to the system which will store the information in a customised database. This automated data entry is designed to reduce human error.

### Measures

#### Sleep studies

A formal home sleep study will be completed when babies are 1 month old. After negotiation with the family, a researcher will visit the home in the evening, and set up the equipment for recording. We plan to use the minimum possible equipment, with the least possible attachments to the baby. Infrared video using a Swann wireless ADW-400 digital camera and recorder, and oximetry using a Massimo Rad 8 set to a 2 second averaging time (analysed using Visi-Download software) will be recorded. Four temperature probes will be used to measure infant toe and core temperature (measured over the liver) and room and outside temperature, using a flat film RTD temperature sensor (5×2 mm). Temperature will be recorded onto GP-HR general purpose 4 channel logger to be attached to the Massimo oximeter.

Video recordings will be viewed off-line using Noldus Observer XT, a software package for the collection, analysis, and presentation of observational data. The data will be coded according to a taxonomy adapted from that used in the Durham University Parent-Infant Sleep Lab (personal communication, [name], Parent-Infant Sleep Lab, Durham University; June 2012). Key categories will include infant sleep time, infant awake time, behavioural arousals, head covering events, breastfeeding events, infant sleep position, and maternal interactions. The software allows synchronisation with physiological recordings of oxygen saturation and temperature. Hypoxic events will be defined as decreases to <90% lasting >10 seconds. Infant peripheral temperature will be used as an indicator of thermal comfort. On the basis of our previous studies
[49] we decided to use a peripheral temperature of <34 degrees as indicating cold stress, or >36 degrees as indicating heat stress. The data will be analysed to identify behavioural events associated with hypoxic episodes or changes in infant temperature.

#### Breastfeeding

Breastfeeding is a primary outcome for this study and information will be gathered from the questionnaires and the overnight sleep study. Participants will be asked at the baseline survey about their knowledge of breastfeeding and their intention to breastfeed. At 1, 3 and 6 months, participants will be asked questions about breastfeeding from which it will be possible to describe the frequency of breasfeeding, full, exclusive or partial breastfeeding, when breastfeeding ceased, and/or when solids or other milk were introduced. They will also be asked about their mothers’ and their partners’ support for, and attitudes toward, breastfeeding. The duration and timing of the breastfeeding episodes will be identified from the sleep study, as well as head covering events during breastfeeding.

#### Biological samples

To measure passive infant exposure to cigarette smoke (cotinine levels), urine will be collected at 1 month during the sleep study by placing a cotton wool ball into the nappy of the baby at each nappy change. Between 3–6 such cotton wool balls will be collected and placed in a 20 ml syringe which will then be squeezed forcing a urine sample into an appropriate container.

To measure salivary oxytocin,
[37, 38], saliva samples will be collected at the baseline, 1 and 3 month visits after 24 hours of abstention from alcohol and salty foods, no brushing or flossing of teeth for 24 hours, and having not consumed drinking water immediately before collecting the sample. Saliva will be gathered in the mouth and then extruded into the appropriate laboratory container via a standard drinking straw.

The saliva samples will be spun, recollected into two cryotubes, frozen on the same day and stored in a local laboratory until delivered to the testing laboratory for analyses of oxytocin. The sample in the second cryotube will be stored until analysed for cotinine. The urine samples will be directly frozen at -40 degrees Celsius until they are analysed for cotinine.

#### Psychological measures

In addition to biological factors, a number of psychosocial factors can influence parenting and infant psychological wellbeing. For example, maternal depression
[40], stress
[52, 53] and environmental chaos
[44] negatively impact infant outcomes, whereas a mother’s mind-mindedness, and the quality of the maternal-infant attachment, predict positive infant outcomes
[54–56]. Data gathered during the questionnaires administered at pregnancy, 3 months, and 6 months, will be used to measure some of the effects of this culturally appropriate intervention on maternal and infant psychological outcomes.

To measure environmental chaos, the Confusion, Hubbub and Order Scale will be administered at baseline
[44]. At baseline and 3 months, social and economic stress will be measured using the questions from the Welsh Family & School Transition Project 2001 ([name], Personal Communication, June, 2007), and social support will be measured using questions from the NSW Child Health Survey
[45]. Maternal depression will be measured using the Edinburgh Postnatal Depression Scale
[47], which will be administered at baseline, 3, and 6 months. Parenting factors will be measured at baseline and 3 months, using questions designed by the authors to measure beliefs about infant care (e.g., 1 = Babies benefit from someone staying with them as they settle to sleep, 5 = Babies benefit by learning to sleep by themselves), as well as items from the Attachment and Adaptation subscales of the Parenting Stress Index
[48]. Maternal mind-mindedness will be measured at baseline, 3, and 6 months, using Likert scale questions designed by the authors (e.g. Baby has his/her own thoughts, 1 = all the time, 5 = None of the time), derived from mind-mindedness research
[57–60]. Maternal mind-mindedness and attachment will also be assessed during pregnancy and at 3 months, by coding a 5 minute audio recording of the mother talking freely about her baby in response to the question, “Could you please tell me what thoughts you have has so far about your (unborn) baby?” The coding system will be based on previous mind-mindedness and attachment research
[57–60].

#### Data analysis

The data will be analysed using modified intention to treat, including only those who completed at least one of the 1, 3 or 6 month visits. Chi-squared tests or Student t-tests will be used to compare the outcomes in the two groups. A per protocol analysis will also be carried out to estimate differences in the outcome variables in those who were compliant with the sleeping arrangement to which they were assigned.

This study will also provide an opportunity to examine factors associated with breastfeeding and sleep practices in a disadvantaged group. The breastfeeding data will be analysed using a discrete time model.

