### Randomisation

Mothers agreeing to participate will be randomised to one of the two groups. Allocation will be concealed and performed, following application of inclusion/exclusion criteria and consent to participate in the study, by opening a sealed envelope opened in numbered sequence. As level of deprivation and parity may significantly affect the primary outcomes, stratified block allocations will be used employing a block size of 3 within each strata combination. Deprivation quintile (derived from home address) of less than 3 versus 3 or more, and parity of 1 versus 2 or more will be used.

After allocation, participant blinding will not be possible. However, the analysis of all overnight studies will, where possible, be performed blind to group allocation. Any measures of parenting that are recorded by audio, will then be analysed blind to group allocation.

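### Randomisation is stratified by deprivation and parity, but the stated tests ignore the strata and the baseline scores: valid and conservative, with precision given away

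*Protocol article*

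**What the plan says.** All references are to the protocol article.

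- **Randomisation:** "As level of deprivation and parity may significantly affect the primary outcomes, stratified block allocations will be used employing a block size of 3". Blocks are formed separately for every combination of the factors, which are given as follows: "Deprivation quintile (derived from home address) of less than 3 versus 3 or more, and parity of 1 versus 2 or more will be used". That makes 2 × 2 = 4 strata.
- **Data analysis:** "Chi-squared tests or Student t-tests will be used to compare the outcomes in the two groups". No strata or covariates are named. The same section adds: "The breastfeeding data will be analysed using a discrete time model". No covariates are listed for that model either, and the text does not say whether it is the main comparison of the arms.
- **Baseline measures:** Outcome measures, Table 1, Biological samples and Psychological measures together collect depression, attachment, mind-mindedness, infant-care beliefs, social support, stress and salivary oxytocin in pregnancy and again after birth. The depression scale, for example, is one "which will be administered at baseline, 3, and 6 months".
- **Use of a baseline value:** the only one stated is under Outcome measures: "Maternal depression and change in depression (from baseline) will be measured at 3 months and 6 months".
- **Breastfeeding:** mothers are also "asked at the baseline survey about their knowledge of breastfeeding and their intention to breastfeed".

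**The concern.** Stratified allocation balances the arms on deprivation and parity, so between-stratum variation is largely removed from the treatment contrast. An unadjusted chi-squared or t-test still counts that variation in its standard error. If the strata are prognostic, which is the reason given for using them, the standard error is larger than it needs to be. The test then rejects less often than its nominal 5% under the null and has less power under the alternative. The design and the analysis do not match.

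A second loss concerns measures taken both in pregnancy and later. A follow-up t-test throws the baseline value away, and a change-score test uses it inefficiently. The trial has about 100 babies per arm and expects 20% dropout by 3 months, so precision that costs nothing is worth having.

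**Working it through.** **1. The plan's own sample sizes rest on unadjusted tests.** Inputs: 45% versus 65% breastfeeding, 80% power, 5% level (two-sided assumed). The two-proportion formula is

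n = [1.96·√(2·p̄(1−p̄)) + 0.8416·√(p₁(1−p₁)+p₂(1−p₂))]² / (p₁−p₂)²

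With p̄ = 0.55 this is [1.96·√0.495 + 0.8416·√0.475]² / 0.04 = 95.9. The continuity correction (n/4)·[1+√(1+4/(n·0.20))]² gives 105.7, so 106 as stated. The same steps for 75% versus 55% in the thermal comfort zone give 98, also as stated.

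**2. Strata ignored, continuous outcome.** Simulation with 5,000 runs per cell, 200 babies and a standardised difference of 0.4. Assumptions not in the documents: 80% in deprivation quintile 3 or more, 60% with parity 2 or more, and the share of outcome variance explained by the strata (R²). Blocks of 4 stand in for 1:1 allocation, because a block of 3 cannot split evenly. Each cell shows unadjusted / adjusted for the two factors.

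| R² | Type I error | Power | Power lost |
|---|---|---|---|
| 0 | 0.050 / 0.050 | 0.806 / 0.805 | none |
| 5% | 0.040 / 0.047 | 0.815 / 0.830 | 1.6 points |
| 10% | 0.038 / 0.049 | 0.814 / 0.840 | 2.6 points |
| 20% | 0.028 / 0.046 | 0.822 / 0.880 | 5.8 points |

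Monte Carlo standard errors are about √(0.05·0.95/5000) = 0.003 for type I error and √(0.8·0.2/5000) = 0.006 for power. As an analytic check, the unadjusted variance is too large by 1/(1−R²), which is 1.11 at R² = 10%. The true size is then P(|Z| > 1.96/√0.9) = P(|Z| > 2.066) = 0.039, against 0.038 simulated.

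Blocks of 3, split 2:1 or 1:2 at random, show the same pattern. Unadjusted type I error is 0.047, 0.042 and 0.032 at R² of 5%, 10% and 20%. Power at 20% is 0.823 / 0.881.

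**3. Strata ignored, binary outcome.** 45% versus 65%, 106 per group, chi-squared / Cochran-Mantel-Haenszel over the four strata, with an assumed odds ratio per factor.

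| Odds ratio | Type I error | Power |
|---|---|---|
| 1.5 | 0.043 / 0.047 | 0.832 / 0.840 |
| 2 | 0.040 / 0.047 | 0.843 / 0.859 |
| 3 | 0.035 / 0.046 | 0.847 / 0.879 |

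The loss is 0.8 to 3.2 power points.

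**4. Baseline score ignored or used as a change.** With baseline-to-follow-up correlation r (assumed), variance relative to a follow-up t-test is 1−r² for baseline adjustment and 2(1−r) for a change score. The ratio of the two is (1+r)/2, which never exceeds 1. Power is at 3 months with 105 × 0.80 = 84 per group, and the effect is set so that the follow-up t-test has 80%.

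| r | Variance, adjusted | Variance, change | Power, adjusted | Power, change |
|---|---|---|---|---|
| 0.3 | 0.91 | 1.40 | 0.836 | 0.658 |
| 0.5 | 0.75 | 1.00 | 0.899 | 0.800 |
| 0.7 | 0.51 | 0.60 | 0.975 | 0.951 |

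Below r = 0.5 the change score is less precise than ignoring the baseline altogether.

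**The case against.** The strongest reply is that this is one short paragraph in a journal article, and that covariate lists belong in a full protocol or analysis plan that is not shown. Nothing in the text rules adjustment out, and the discrete time model can carry covariates. This stands in part: it would be wrong to say that every outcome is fixed to an unadjusted test. But the article does name its tests, and those tests do not match its own reason for stratifying.

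The assumed inputs are also open to challenge. The Randomisation section says only that the factors may matter. Recruitment is from areas of high deprivation, so the deprivation split may be uneven and explain little. A score about an unborn baby, or oxytocin in pregnancy, may correlate weakly with later values; at r = 0.1 to 0.2 the variance reduction is r² = 1 to 4%. That is fair, and it is why ranges are shown. If the strata explain nothing, adjustment costs nothing measurable.

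Four stronger readings are tempting, and the documents do not support them:

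- **That the p-values are invalid.** The error is on the conservative side only; type I error is not inflated.
- **That the 9 to 49% gain applies to the primary outcomes.** The sleep-study and breastfeeding outcomes have no baseline value, because the infant is not yet born.
- **That adjustment repairs breastfeeding power.** Power by the uncorrected formula falls from 0.838 at 106 per group to 0.745 at the 84 left after 20% dropout. A gain of 1 to 3 points does not make that up.
- **That adjustment rescues the no-difference safety hypothesis.** That hypothesis lacks a margin, which is a separate matter. The Contamination section analyses safety outcomes by the device actually used, where confounding is the larger problem and the argument about stratified allocation does not carry over cleanly.

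The change-score criticism reaches depression only, and the follow-up depression score is listed alongside it.

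**Conclusion.** The point holds as a loss of efficiency and a mismatch between design and analysis; it is not a validity error. Under an assumed 5 to 20% of variance explained by the strata, the unadjusted comparison of a continuous outcome has type I error of about 0.04 to 0.03 and gives up about 2 to 6 power points. Binary outcomes give up about 1 to 3 points at assumed odds ratios of 1.5 to 3 per factor. For depression, attachment, mind-mindedness, infant-care beliefs, social support, stress and oxytocin, baseline adjustment lowers variance by r² against a follow-up t-test (9 to 49% for an assumed r of 0.3 to 0.7, less if r is lower) and is never less precise than a change score. None of these strengths is given in the documents. The improvement is worth making because it is nearly free, although for the binary primary outcomes it is modest.

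**What to change.** In the Data analysis section, replace the sentence on chi-squared and t-tests with the following, fixed before outcomes are compared by arm:

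- Binary outcomes: the main comparison is a Mantel-Haenszel risk difference stratified by the two randomisation factors.
- Continuous outcomes: a linear model with the two factors, plus the baseline value of the same measure where one exists, in place of a change-score test.
- Breastfeeding: include the two factors in the discrete time model.
- Keep the unadjusted tests as supportive analyses.

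Adjustment for intention to breastfeed or maternal smoking is optional. Do not use logistic models for rare events. Head covering is expected in about 3% of bassinet babies, so with 100 per arm and no difference there would be about 3 + 3 = 6 events, too few for several covariates.

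The cost is a change of wording and a few lines of code. The factors and baseline scores are already collected.
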